### Follow-up

All included participants will be re-evaluated at 6 and 12 months through phone calls or as outpatients.

### Statistics

#### Sample size

This study will be a trial of a new therapeutic regimen of KLX treatment. The sample size was calculated using software PASS based on a similar study on a Chinese herbal medicinal supplement conducted previously [20, 21]. According to the results of our previous trial, the mean decline of eGFR in the expected population was assumed to be 1.38 ± 3.21 and 2.61 ± 3.16 ml/min/1.73 m^2^/half a year in losartan potassium plus KLX versus losartan potassium plus placebo group, respectively. Therefore, we estimated that with a sample size of 105 patients assigned to each group (ratio 1:1) would be sufficient to achieve 90% power in detecting the differences of the primary endpoint based on a two-sided level of significance of 5%. Allowing for a 20% withdrawal rate, we plan to include 126 patients in this trial.

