### Study settings and recruitment

Assuming a 20% dropout rate, a total of 252 patients will be recruited from the eighteen centers mentioned above using posters, the hospitals’ websites, and networks from December 2019 to December 2020. Research assistants will manage the recruitment, and endocrinologists will diagnose the participants. On the consent form, participants will be asked for permission to apply their data in case of withdrawal. Participants will also be asked to agree to share the research data with people from the hospitals participating in the study or from regulatory authorities where relevant. Biological specimens are not stored in this study. The trial adopted clinical trial insurance, and affected participants will receive appropriate coverage if serious harm occurs following the trial.

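### The stated 90% power does not follow from the protocol's own inputs: 105 patients per group gives about 80%

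*Protocol article*

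**What the plan says.** All the inputs stand in one paragraph of the protocol article (Statistics, Sample size). It says that "the mean decline of eGFR in the expected population was assumed to be 1.38 ± 3.21 and 2.61 ± 3.16" ml/min/1.73 m² per half year, for losartan plus Keluoxin and losartan plus placebo respectively, citing the group's previous trial. From this it concludes that "a sample size of 105 patients assigned to each group (ratio 1:1) would be sufficient to achieve 90% power", at a two-sided 5% level. The software named is PASS.

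The same paragraph then inflates for loss: "Allowing for a 20% withdrawal rate, we plan to include 126 patients in this trial". The Abstract shows that 126 is the number per group, and Study settings and recruitment gives the total: "Assuming a 20% dropout rate, a total of 252 patients will be recruited".

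The Data analyses section specifies a repeated-measures analysis of covariance for the primary outcome, with baseline eGFR as covariate. The sample size paragraph mentions no correlation, no repeated-measures gain and no variance reduction.

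**The concern.** Two means, two SDs, a significance level and a group size fix the power of a two-sample comparison. Here the standardised effect is about 0.39, and 105 per group looks too few for 90% power at that effect.

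This is the primary endpoint of a superiority trial. If the power is overstated, the chance of missing the planned effect is larger than readers are told. A non-significant result would then be read as the failure of a 90%-powered trial, and so as stronger evidence against a benefit of 1.23 than the design supports. The error does not bias the treatment estimate and does not change the type I error.

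**Working it through.** **Inputs** (all from Statistics, Sample size)
- Mean declines: 2.61 (placebo) and 1.38 (Keluoxin), so the difference is 2.61 − 1.38 = 1.23.
- SDs: 3.21 and 3.16. Sum of variances: 3.21² + 3.16² = 20.29. Pooled SD: √(20.29/2) = 3.185.
- Standardised effect: 1.23/3.185 = 0.386.
- Two-sided 5%, 1:1 allocation, 105 per group.

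**Attempt to reproduce the stated 90%**

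The standard error of the difference at 105 per group is √(20.29/105) = 0.4396. The expected z is 1.23/0.4396 = 2.798. Normal-approximation power is Φ(2.798 − 1.960) = 79.9%. The exact noncentral t calculation gives 79.5%. The stated 90% is not reproduced.

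**Group size for each power level**

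n per group = (z₁₋α/₂ + z₁₋β)² × (SD₁² + SD₂²) / difference², with 1.23² = 1.513.
- 80%: (1.960 + 0.842)² × 20.29/1.513 = 105.3
- 90%: (1.960 + 1.282)² × 20.29/1.513 = 140.9

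Rounded up, these are 106 and 141. The noncentral t needs 107 and 142. The printed 105 is, to rounding, the 80% figure.

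**Do other readings recover 90%?**

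| Reading | Result |
|---|---|
| One-sided 5%, 105 per group | 87.4% (t), 87.6% (normal) |
| Two-sided 5%, all 126 per group, no loss | 86.3% (t), 86.5% (normal) |
| Either SD alone (3.16 or 3.21) | 139 or 144 per group needed for 90% |
| Means and SDs both annualised | effect size unchanged, so power unchanged |
| Rank test instead of t test | more patients needed, not fewer |

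Only a one-sided test combined with all 126 per group and no loss passes 90% (92.1% by t). That departs from the text twice: the protocol says two-sided throughout and attaches the 90% to 105.

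**What 105 per group can do**

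The difference detectable with 90% power is 1.43 by the t test; the normal formula gives 3.185 × √(2/105) × (1.960 + 1.282) = 1.42. For 90% power at a difference of 1.23, the residual SD would have to be about 2.74. Since 1 − (2.74/3.185)² ≈ 0.26, baseline adjustment would have to remove about 26% of the variance, a correlation of about 0.51 with the change in eGFR.

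**Loss to follow-up**

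126 is 105 × 1.2. A 20% loss from 126 leaves 126 × 0.8 = 100.8, about 101 per group, where power is 78.0% (t). Dividing instead, 105/0.8 = 131.25, so 132 per group would be needed to keep 105.

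**The case against.** The arithmetic is hard to dispute. The best counter-arguments concern cause and consequence.

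*The cause is not proven.* An 80% calculation labelled 90% is the simplest explanation, but 105 falls just short of 80% under both formulas. A misprinted input is also possible: a common SD of about 2.74 would give 90% at 105 per group. This stands. The document shows that inputs, group size and power disagree; it does not show which one was mistyped. As printed, though, the 90% is wrong.

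*The planned analysis is stronger than an unadjusted test of 105 per group.* The primary model adjusts for baseline eGFR, and the full analysis set keeps dropouts through imputation, so up to 126 per group may be analysed. At 126, removing about 11% of the variance (correlation about 0.34) would be enough for 90%. This stands in part: the power of the final analysis could exceed 80%. But imputed patients carry less information than completers, and the sample size paragraph derives its 90% from the raw means and SDs at 105 per group. If a gain from adjustment was relied on, the paragraph needs to say so.

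*It is only a wording change, and 80% power is commonly accepted.* True, and that makes the correction cheap. It does not make the printed figure right.

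**Conclusion.** The concern holds. On the protocol's own means, SDs, significance level and group size, power is about 80% (79.5% by t, 79.9% by normal approximation), not 90%. The type II error is about 20% rather than 10%. For 90% power, 142 evaluable patients per group would be needed, 37 more than the 105 stated.

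This rests on an unadjusted two-sample comparison of means, which is the only calculation the stated inputs support. It describes the sample size statement; the baseline-adjusted model may do better by an amount the document does not give. Because the misstatement concerns the primary endpoint and doubles the stated risk of missing the planned effect, it must be corrected.

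**What to change.** First check the PASS output to confirm that the means, SDs and group size are printed as entered. If they are, restate the paragraph: 105 evaluable patients per group gives about 80% power at two-sided 5% for a difference of 1.23 per half year, and 90% power only for about 1.43. Use the corrected figure in the final report, and in the registry entry if it states a power. In the same edit, say that 126 is the number per group and that a 20% loss from 126 leaves about 101 per group, with power of about 78%.

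If an input was misprinted, or a variance reduction from baseline adjustment was assumed, correct or state that instead and show that 90% then follows.

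The cost is wording only, with a less favourable stated power and no extra enrolment. If the sponsor wants to keep 90% for 1.23, that is a separate decision: 142 evaluable per group, or 142/0.8 = 177.5, so 178 randomised per group (356 in total) against the planned 252.

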**Methods:**

We will conduct a randomized double-blind placebo-controlled multicenter clinical trial. A total of 252 participants diagnosed with DKD recruited from 18 institutions will be randomly allocated to either a losartan potassium plus KLX (*n* = 126) or a losartan potassium plus placebo group (*n* = 126). The participants will be administered KLX or placebo in addition to losartan potassium for 24 weeks. The primary outcome measure will be the decline in estimated glomerular filtration rate (eGFR) (ml/min/1.73 m^2^/year) from baseline within 24 weeks, and the secondary outcomes will be the incidence of serum creatinine doubling, the incidence of end-stage renal disease (ESRD), the proportion of subjects with a progressive decline in eGFR > 30%, the percent change in 24 h urinary total protein (UTP), the change in the urinary albumin/creatinine ratio (UACR), and the total effective rate of the traditional Chinese medicine (TCM) syndrome scale scores. Comparison of the differences in the variables between groups will be performed according to the data revealed by independent *t* tests, chi-squared tests, Fisher’s exact tests, or Wilcoxon’s tests. All statistical tests will be two-sided, and significance will be considered for *p* values < 0.05.

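### The 20% dropout allowance is applied as 105 × 1.2, so 126 per group leaves about 100 after the assumed loss, not the 105 it was meant to protect

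*Protocol article*

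**What the plan says.** The Sample size section under Statistics plans on mean eGFR declines, with standard deviations, of "1.38 ± 3.21 and 2.61 ± 3.16 ml/min/1.73 m^2^/half a year" for the KLX and placebo groups. It asserts that "a sample size of 105 patients assigned to each group (ratio 1:1") is "sufficient to achieve 90% power in detecting the differences of the primary endpoint" at a two-sided 5% level. It then makes the dropout adjustment: "Allowing for a 20% withdrawal rate, we plan to include 126 patients in this trial".

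Study settings and recruitment repeats the allowance and ties it to those recruited: "Assuming a 20% dropout rate, a total of 252 patients will be recruited". The Methods paragraph of the Abstract shows how the total divides: "losartan potassium plus KLX (*n* = 126) or a losartan potassium plus placebo group (*n* = 126"). The Discussion also gives 252. No section offers another dropout rate or another rule for the adjustment.

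**The concern.** The allowance exists so that the required number is still there once the expected share of patients has left. That means dividing the required number by the retained fraction. Adding 20% to the required number is a different operation and falls short, because the 20% is then lost from the larger enrolled number.

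The number behind the power statement is therefore not delivered under the protocol's own assumption. This is independent of whether 105 was the right starting point: correcting either step leaves the other wrong.

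The sentence also gives 126 as the number in the trial. Read literally, that is half the size stated everywhere else.

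**Working it through.** **Inputs**
- Required per group: 105 (Sample size).
- Withdrawal rate: 20% (Sample size; Study settings and recruitment).
- Planned: 126 per group, 252 in total (Abstract, Methods; Study settings and recruitment).
- Difference in mean decline: 2.61 − 1.38 = 1.23 ml/min/1.73 m² per half year (Sample size).
- Standard deviations: 3.21 and 3.16 (Sample size). Pooled: √[(3.21² + 3.16²) / 2] = 3.185.
- Two-sided 5% test, 1:1 allocation.

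**Step 1: reproduce the plan's figure.** n × (1 + d) = 105 × 1.20 = 126 exactly. Since the match is exact, rounding does not explain the figure.

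**Step 2: the figure that keeps 105.** n / (1 − d) = 105 / 0.80 = 131.25, rounded up to 132 per group, or 264 in total. This is 6 more per group and 12 more overall than planned.

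**Step 3: what 126 delivers.**
- Remaining after a 20% loss: 126 × 0.80 = 100.8 per group, which is 4 to 5 short of 105. Over the whole trial, 252 × 0.80 = 201.6 against 210.
- Loss that 126 can absorb: 1 − 105/126 = 16.7%.

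**Step 4: effect on power.** For a two-sample t test with n per group, the noncentrality is 1.23 / (3.185 × √(2/n)) on 2n − 2 degrees of freedom.

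| n per group | Meaning | Power (t test) |
|---|---|---|
| 100 | 126 less 20%, rounded down | 77.6% |
| 101 | 126 less 20%, rounded up | 78.0% |
| 105 | number the plan calls for | 79.5% |
| 126 | no loss at all | 86.3% |
| 132 | matching figure, before any loss | 87.8% |

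The dropout step costs 79.5 − 78.0 = 1.5 to 79.5 − 77.6 = 1.9 percentage points.

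**Step 5: relation to the 90% claim.** On the same inputs, 90% power needs 141 per group (normal approximation) or 142 (t test). Dividing by 0.8 gives 176.25 and 177.5, so 177 or 178 enrolled per group. The 132 of Step 2 repairs the dropout step only.

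**The case against.** Four points can be made for the plan.

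**The effect is small.** Tolerating 16.7% rather than 20% lies within the uncertainty of any dropout guess, and about 2 points of power is modest. That is true, and it limits the weight of the point. The stated figures still do not agree with one another.

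**Withdrawn patients stay in the primary analysis.** Data analyses makes intention-to-treat primary, keeps dropouts in the full analysis set and fills missing primary-outcome data by last observation carried forward, with multiple imputation also named. About 100 per group is therefore closer to a completer count than to the number analysed. In addition, the planned model is a repeated-measures analysis of covariance adjusting for baseline eGFR, so the t-test figures above check the planning calculation and are not the power of the planned analysis. This part stands. It does not rescue the allowance, whose only purpose was to preserve 105 after withdrawals. Carried-forward or imputed values do not bring back the missing week-24 measurements, and the supporting per-protocol analysis loses those who withdraw.

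**Multiplying by 1.2 is a common shortcut.** It still does not leave 105 when 20% of those recruited drop out, and Study settings and recruitment attaches the rate to recruitment.

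**The number 105 is itself unsound.** This is correct: the stated inputs do not give 90% power at 105 per group. The number is required only because the protocol says so, and a sponsor who simply adopted 132 would still have about 80% power after a 20% loss. This is a reason to correct both steps together.

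The wording that puts 126 in the whole trial is an editorial slip, resolved by the other sections, and adds no weight to the arithmetic.

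**Conclusion.** The point holds. The dropout adjustment is wrong as written: 126 per group leaves 100.8 after the stated 20% loss, 4 to 5 below the 105 it was meant to secure, and it covers a loss of only 16.7%. Taken alone the consequence is modest, about 1.5 to 2 points of power, from 79.5% to about 78%.

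The conclusion assumes that the 20% is a share of those enrolled, which is how the article uses it, and that 105 means patients remaining after withdrawal. The power figures further assume the planning difference and standard deviations, an unadjusted two-sided t test, and no information from patients who withdraw. The power shortfall of 105 against the claimed 90% is a separate and larger error.

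**What to change.** In Sample size, state that 126 is the number per group and 252 the total. Then take one of these routes:

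1. Keep the planned size and say that 126 per group allows for a 16.7% loss down to 105.
2. Keep the 20% rate and say that about 100 per group would remain, with about 78% power for the planning difference.
3. Keep the claim of 105 completers at 20% loss and give the matching size, 132 per group (264 in total).

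Under route 1 or 2, make the dropout sentence in Study settings and recruitment agree. The first two routes cost only wording. The third adds 12 patients and still leaves power near 80% after the assumed loss, so it should not be presented as restoring 90%. Whichever is chosen, correct the 90% power statement in the same revision, so that required number, dropout rate, enrolled number and power all follow from one calculation.

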#### Data analyses

The independent researchers performing the biochemical tests, assessing the clinical outcomes, and analyzing the data will be kept blinded to the patients’ identities and grouping.

Continuous indicators are described as means, standard deviation, medians, and interquartile ranges, while classification variables are reported as absolute values and percentages. The following aspects should be analyzed at the end of the trial: the actual number of participants in the two groups, dropped and excluded cases, baseline characteristics, compliance, efficacy, and safety. To insure the comparability between groups, baseline comparisons, including the indicators of demographic characteristics, clinical characteristics, biochemical variables, medical history, and medication history (Tables 2 and 3), were performed according to the data features by independent *t* test, chi-squared test, or Fisher’s exact test.

**Table 2 Tab2:** List of baseline characteristics of participants

Category	Items
Demographic characteristics	Age
	Sex
Clinical characteristics	Known duration of diabetes
	CKD stage
	Body mass index (height and weight)
	Blood pressure
Biochemical variables	eGFR, Scr
	UACR, 24 h UTP
	TC, TG, HDL-C, LDL-C
	ALT, AST, ALP, TBIL, GGT
	PT, APTT, FIB
	Blood glucose
	Glycated hemoglobin
Medical history	Hypertension
	Hyperlipidemia
	Coronary heart disease
	Congestive heart disease
	Stroke
	Peripheral vascular disease
	Others
Medication history	Drug name
	Drug dose
	Beginning drug use date
TCM evaluation scores	Details are listed in Table 3

**Table 3 Tab3:** Traditional Chinese medicine (TCM) symptom assessment survey and evaluation standard

Signs/symptoms		Score				Scores
		Normal: 0	Mild: 2	Moderate: 4	Severe: 6	
Primary signs/symptoms	Dry mouth and throat	None	Decreased saliva production	Moderate thirst relieved by drinking fluids	Severe thirst with constant need to drink fluids	
	Fatigue	None	Cannot sustain heavy work	Can manage mild intensity work	Can only perform daily activities	
Secondary signs/symptoms	Prone to be hungry and eat more	None	Easy to be hungry	Easy to be hungry and unbearable hunger	Unbearable hunger and hypoglycemia	
	Shortness of breath	None	Shortness of breath after mild activity	Shortness of breath after moderate activity	Unable to talk or catch breath even without activity	
	Heat sensation in chest, palms, and soles	None	Heat sensation in palms and soles at night	Moderate heat sensation in chest, palms and soles	Severe heat sensation in chest, palms, and soles and desire to expose body	
	Fixed pain in the chest, lower back, or limbs	None	Occasional and relieved spontaneously within half an hour	Less than three hours a day, relieved by common drugs	Continuously fixed pain, relieved only by painkillers	
	Numbness of the limbs	None	Tips of hands and feet	Hands and feet	Limbs	
Tongue and pulse	Tongue	Dark red tongue with less fluid coating; others (description):				
	Pulse	Weak and thin pulse; others (description):				

Manifestation of tongue and pulse is only for reference without being calculated in the scores

Evaluation standard of total effective rate of TCM syndrome scale score

(1) Clinical recovery: the clinical symptoms and signs disappear or basically disappear, and syndrome scores are reduced by ≥ 95%

(2) Significantly effective: the clinical symptoms and signs are significantly improved, and syndrome scores are reduced by ≥ 70%

(3) Effective: the clinical symptoms and signs are improved, and syndrome scores are reduced by ≥ 30%

(4) Invalid: the clinical symptoms and signs are not improved, or even worsened, and syndrome scores are reduced by less than 30%

The calculation formula (Nimodipine method) is as follows: [(scores before treatment − scores after treatment) ÷ scores before treatment] × 100%

Total effective rate = (clinical recovery + significantly effective + effective) number of cases/total number of cases × 100%

The total effective rate of the KLX group and the control group after treatment is calculated and compared

Full Analysis Set (FAS), Per Protocol Set (PPS), and Safety Set (SS) are to be used for data analysis. According to intention-to-treat principle, FAS is defined as analysis of all cases who met all the inclusion criteria and none of the exclusion criteria, were randomized, and had at least one dose of the study drug. It included all enrolled and dropout cases except excluding participants. Multiple imputation analysis will be carried to explain the effect of missing data. Missing data of the primary outcomes will be carried forward with the principle of the last observation carried forward (LOCF). PPS includes the data from the subjects who follow the test protocol strictly, have good compliance, do not take the prohibited drugs during the test period, and complete the CRF form. SS refers to the participants who have made at least one visit and actual data recorded for safety indicators.

To evaluate the effect of KLX, data were analyzed primarily using an intention-to-treat principle, and per-protocol analysis served as a supplement. For the primary outcomes, we will calculate the changes of eGFR from baseline. To compare the decline in eGFR between two groups, repeated-measures analysis of covariance model will be performed using baseline eGFR as covariates. Least-square means with SEMs and two-sided 95% CIs for differences between groups were estimated. For secondary outcomes, statistical description and comparison between groups will be performed according to whether the variables are continuous or categorical data. To be specific, the difference in classification indicators among secondary outcomes, including the incidence of Scr doubling, the incidence of ESRD, and the proportion of subjects with a progressive decline in eGFR of > 30% from baseline within 24 weeks, between groups will be compared using chi-squared or Fisher’s exact test. While the difference in the total effective rate of TCM syndrome scale scores between the two groups will be tested as rank data using Wilcoxon’s test or CMH test. Comparison of the continuous variables, such as the percent change in 24-h UTP and the change in UACR, will be performed applying independent *t* tests (or the Mann-Whitney *U* test). Safety evaluation is composed of comparison of parameters listed above as well as adverse events evaluation. Besides the detailed description, reason, and explanation of the adverse events, the chi-squared test or Fisher’s exact test will be used to compare the incidence of AEs between the two groups.

There will be no interim analysis of the data because there are no anticipated problems that are detrimental to the participants. All the data will be analyzed using Statistical Package for the Social Sciences (SPSS) version 17.0 (SPSS, Inc., Chicago, IL) software. All statistical tests will be two-sided, and significance will be considered for *p* values < 0.05.

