### Randomization, allocation concealment, and blinding

The participants will have an individual trial identification number and be randomly assigned to either the losartan potassium plus KLX group or the losartan potassium plus placebo group in a 1:1 ratio. Randomization will be performed using Statistics Analysis System (SAS) software by an independent statistical agency. The Data Management Center of Guang’anmen Hospital will be responsible for drug blinding and randomization concealment. The statistician will not participate in the randomization and will analyze the collected data without having access to allocation information. Research assistants will enroll patients at the 18 participating medical centers sequentially on the basis of screening order. Both the participants and the investigators will be kept blinded to the allocations until the trial is completed. In case of a severe adverse event, an administrator at the Data Management Center of Guang’anmen Hospital will unblind the patient information as an emergency measure and provide appropriate treatment.

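### Baseline significance tests cannot show that randomised arms are comparable; describe baseline by arm and prespecify log(UACR) beside baseline eGFR in the primary model (minor)

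*Protocol article*

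**What the plan says.** The Data analyses section plans baseline comparisons between the arms and gives their purpose: "To insure the comparability between groups, baseline comparisons, including the indicators of demographic characteristics, clinical characteristics, biochemical variables, medical history, and medication history". These comparisons, on the variables of Tables 2 and 3, "were performed according to the data features by independent" t test, chi-squared test or Fisher's exact test. Table 2 is headed "List of baseline characteristics of participants". The same section sets one level for everything: "All statistical tests will be two-sided, and significance will be considered for" p-values below 0.05.

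The Randomization section allocates patients to the KLX group or the "losartan potassium plus placebo group in a 1:1 ratio". For the primary outcome, a "repeated-measures analysis of covariance model will be performed using baseline eGFR as covariates". No other covariate is named. The section also provides for descriptive summaries (means, standard deviations, medians, interquartile ranges, counts and percentages).

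**The concern.** A significance test asks whether a difference could be due to chance. After proper randomisation, chance is the only source of a baseline difference, so the null hypothesis is true by design. A significant result then says nothing about whether the arms were fairly formed. A non-significant one does not show that an observed difference is small enough to ignore, and the article states no size of difference that would matter. The stated purpose is therefore out of reach of the stated method.

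Two things are at stake. A sound trial will probably show at least one significant baseline difference, which may cast doubt on a valid randomisation. And the tool that does deal with chance imbalance, prespecified adjustment for prognostic baseline variables, is applied to baseline eGFR only. UACR is an entry criterion, is listed in Table 2, and belongs to the feature (proteinuria) by which the Background characterises the disease alongside declining renal function.

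**Working it through.** **Inputs from the article.** Randomised: 126 per arm ("A total of 252 participants diagnosed with DKD recruited from 18 institutions will be randomly allocated", 1:1). Evaluable: 105 per arm. Assumed declines: "1.38 ± 3.21 and 2.61 ± 3.16 ml/min/1.73 m^2^/half a year". Significance level: two-sided 5% for all tests.

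**Number of baseline items.** The article gives no count. From Table 2: age and sex (2); diabetes duration, CKD stage, BMI, systolic and diastolic pressure (5); biochemical variables (18: eGFR, Scr, UACR, 24 h UTP, four lipids, five liver indices, three coagulation indices, glucose, HbA1c); named histories (6); total TCM score (1). The sum is 2 + 5 + 18 + 6 + 1 = 32. It is 31 if blood pressure counts once, and about 40 if other histories, medication items or single symptoms are tested.

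**Chance of at least one significant difference under correct randomisation.**
- Expected number: 32 × 0.05 = 1.6.
- Independent items: 1 − 0.95^32 = 1 − 0.194 = 0.806. With 31 items 0.796; with 40 items 0.871.
- Correlated items (simulation of 32 equally correlated normal test statistics):

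| Common correlation | P(at least one p < 0.05) |
|---|---|
| 0.1 | 79% |
| 0.2 | 75% |
| 0.3 | 68% |
| 0.5 | 52% |

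- With correlated blocks of related laboratory variables and conservative Fisher tests for the six histories: about 71% to 76%.

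The probability exceeds one half in every 32-item scenario.

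**The plan's own power figure.** This is needed as a starting point for the covariate.
- Difference: 2.61 − 1.38 = 1.23. Pooled SD: √((3.21² + 3.16²)/2) = 3.185.
- Standard error at 105 per arm: 3.185 × √(2/105) = 0.440. Ratio: 1.23/0.440 = 2.80.
- Power: Φ(2.80 − 1.96) = 0.80. The article states 90% for 105 per arm, which is not reproduced; 90% needs 141 per arm. That is a separate matter, and 80% is used below.

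**What adding log(UACR) could gain.** Let r be the correlation of baseline log(UACR) with eGFR decline that remains after adjusting for baseline eGFR. The documents give no value, so r is an assumption, shown from 0.1 to 0.5. Residual variance is multiplied by 1 − r², and power is Φ(2.80/√(1 − r²) − 1.96). The planning SD is taken as the residual SD before UACR is added.

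| Assumed r | Fall in residual variance | Power at 105 per arm |
|---|---|---|
| 0.1 | 1% | 80% |
| 0.3 | 9% | 83% |
| 0.5 | 25% | 90% |

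**The case against.** The strongest reply is that this changes nothing in the inference. The article does not say that a baseline p-value will add or drop a covariate, alter an analysis set or qualify a conclusion. The primary covariate is fixed in advance. Adjusting for the baseline value of the outcome is a standard and valid ANCOVA, and randomisation protects the comparison whether or not UACR is in the model. Chance imbalance is ordinary sampling variation, which the 95% confidence interval already covers. Further covariates may also be left to a full analysis plan that is not shown.

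All of that stands, and it limits the point to a minor one. It does not rescue the stated purpose of the tests, which is written in the article and cannot be met. Nor does it remove the possible precision gain, which is why the UACR covariate is offered as an improvement and not as the repair of an error.

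A reader might also infer that the tests let through about half of the imbalances large enough to matter. The documents do not support such a figure. Computing it as type II error assumes a true population difference at baseline, which randomisation excludes. A chance imbalance is an observed difference: at 126 per arm, one of 0.25 SD gives t = 0.25 × √(126/2) = 1.98, p about 0.048, so it is flagged. The share of consequential imbalances that go unflagged depends on a prognostic correlation and a threshold that the article does not give.

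**Conclusion.** The point holds as a minor one. The baseline tests cannot establish comparability, and under correct randomisation they will probably yield at least one significant result: about 81% if the 32 items are independent, and 52% at a common correlation of 0.5. This rests on a count made from Table 2 and on assumed correlations among the items.

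Two stronger readings are not supported. One is that eGFR-only adjustment biases the primary result: leaving out UACR can cost precision but leaves the randomised comparison valid. The other is that baseline p-values will steer the analysis: nothing in the article says so. The size of the precision loss is unknown. It ranges from negligible (r = 0.1) to about ten percentage points of power (r = 0.5), and that range is assumed.

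**What to change.** In Data analyses, remove the baseline significance tests and the comparability purpose attached to them. Present the Table 2 and Table 3 variables by arm with the descriptive summaries that the section already lists, without p-values.

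In the description of the primary analysis, name baseline log(UACR) beside baseline eGFR as a covariate in the repeated-measures ANCOVA, to be included whatever imbalance is observed. Add that no covariate will be added or dropped on the basis of a baseline p-value. The log scale is suggested because entry requires at least 30 mg/g and sets no upper limit, so a right-skewed distribution is likely.

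The cost is wording and one degree of freedom. UACR has to be measured for entry, so no new data are needed.
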